## 2 LIST OF ABBREVIATIONS

|         |                                                     |
|---------|-----------------------------------------------------|
| AE      | Adverse event                                       |
| AUDIT-C | Alcohol Use Disorders Identification Test           |
| BID     | Twice a day                                         |
| CO      | Carbon monoxide                                     |
| CPD     | Cigarettes per day                                  |
| CRC     | Clinical Research Coordinator                       |
| CSC     | Center for Smoking Cessation                        |
| CTA     | Clinical Trials Assistant                           |
| DSCP    | Duke Smoking Cessation Program                      |
| DSMB    | Data and Safety Monitoring Board                    |
| DUHS    | Duke University Health System                       |
| EMR     | Electronic medical record                           |
| FDA     | Food and Drug Administration                        |
| FTND    | Fagerström Test of Nicotine Dependence              |
| GAD-2   | Generalized Anxiety Disorder 2-item Scale           |
| GCP     | Good Clinical Practice                              |
| ICS     | Investigational Chemotherapy Service                |
| IRB     | Institutional Review Board                          |
| NIDA    | National Institute on Drug Abuse                    |
| NIH     | National Institutes of Health                       |
| MPSS    | Mood and Physical Symptoms Scale                    |
| P       | Placebo (e.g. P-Varenicline is Placebo Varenicline) |
| PHI     | Protected Health Information                        |
| PHQ-9   | Patient Health Questionnaire-9                      |
| PSS-4   | Perceived Stress Scale                              |
| SAE     | Serious adverse event                               |
| TQD     | Target Quit Day                                     |

### 3 PROTOCOL SYNOPSIS AND RESEARCH SUMMARY

#### 3.1 Purpose

The purpose of this study is to assess an “adaptive” approach to smoking cessation pharmacotherapy. The protocol is designed to compare adaptive vs. standard approaches to two common smoking cessation pharmacotherapies (Varenicline and Nicotine Patch). The adaptive treatment approach provides the addition of Bupropion in the pre-quit period for participants who are not “responding” to initial treatment. Little is known about the adaptive use of Varenicline or Nicotine Patch, in which Bupropion is added to Varenicline or Patch for those who do not respond to one of these medications in a pre-quit treatment period. This study attempts to address these knowledge deficits. The study (N=300) is a double-blinded randomized placebo-controlled trial designed to compare biochemically-confirmed abstinence rates in smokers randomized to Varenicline Adaptive Protocol vs. Varenicline (N=150) and for comparison, Nicotine Patch Adaptive Protocol vs. Nicotine Patch (N=150). The “Varenicline Adaptive Protocol” is conducted by starting treatment with Varenicline 4 weeks prior to the quit day, then following each participant’s response to this pre-treatment medication. After 2 weeks, if the patient shows a reduction greater than 50% in cigarettes smoked per day then the patient is considered to be a “Varenicline responder” and is continued on Varenicline alone out to 12-weeks post quit day. If the patient does not spontaneously decrease smoking in the pre-quit period by more than 50% cigarettes per day, the patient is considered to be a “Varenicline non-responder” and Bupropion is added to the Varenicline. For comparison, an identical protocol is used with nicotine patch vs. nicotine patch adaptive treatment. The study uses only FDA-approved medications: Varenicline, Nicotine Patch, Bupropion, and placebo controls. To pattern clinical practice, participants will be able to choose whether they would like to use a patch or Varenicline-based treatment. After choosing, however, they will be randomized to adaptive vs. non-adaptive version of that treatment. Placebo medications are matched throughout the study. Participants will be blinded to all medications. All participants will receive behavioral treatment including a single 40-minute visit with a medical provider. The study is designed to provide researchers and clinicians with a better understanding of how to use adaptive pharmacotherapy protocols to improve smoking cessation rates.

#### Primary Objective

1. Biochemically-confirmed 30-day continuous smoking abstinence at 12-weeks post quit attempt measured by self-report and confirmed by carbon monoxide (CO) expired breath testing with CO < 7ppm required to confirm abstinence. Subject will be coded as abstinent only if he or she meets criteria for both self-reported abstinence and biochemical abstinence.

#### Secondary Objectives

2. To compare 7-day point prevalence biochemically confirmed abstinence rates at 2- and 12-weeks post-TQD in participants randomized to adaptive vs standard treatment.
3. To compare phone-assessed self-reported abstinence at 1, 2, 6, 12, 26 and 52 weeks post-TQD in participants randomized to adaptive vs standard treatment. Phone assessments will be compared at specific time points and also across multiple time points using multi-level modeling.
4. To compare smoking reduction (number of cigarettes per day) at 2 and 12 weeks post TQD in participants randomized to adaptive vs standard treatment.
5. To compare smoking reduction (number of cigarettes per day) on phone-based self-report at 1, 2, 6, 12, 26, and 52 weeks post-TQD in participants randomized to adaptive vs. standard treatment. Phone assessments will be compared at specific time points and also across multiple time points using multi-level modeling.

#### Exploratory Objectives

6. To assess potential baseline (pre-intervention) predictors of abstinence including self-reported dependence, stress, anxiety, depression, alcohol and drug use, and self-efficacy. If a baseline variable is found to be associated with abstinence, it will be further assessed as a moderator of abstinence.
7. To assess change in self-reported measures at baseline (pre-quit) to 2- and 12-weeks post TQD on repeated standardized measures of nicotine dependence, stress, anxiety, depression, alcohol and drug use, and self-efficacy. If a measure is found to change significantly from baseline to a post quit time point, it will be assessed as possible mediator of abstinence outcomes.
8. To compare phone-assessed non-standardized single item questions on urges, withdrawal, motivation to quit smoking or remain abstinent, and confidence in ability to quit or remain abstinent at 1, 2, 6, 12, 26 and 52 weeks post-TQD. If a measure is found to change significantly from baseline to a post quit time point, it will be assessed as a possible mediator of abstinence outcomes. Phone assessments will be compared at specific time points and also across multiple time points using multi-level modeling.

9. To compare baseline scores on anxiety, depression, and stress for their effect on allocation to Responder or Non-Responder status in the adaptive and standard treatment arms.
10. To conduct cost-benefit analyses on allocation to adaptive vs standard treatment from the perspective of multiple stake holders: smokers, healthcare systems (clinics/hospitals), insurance companies, and employers.

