#### **Exploratory Objectives**

6. The following baseline self-report assessment outcomes will predict biochemically confirmed 30-day continuous abstinence at 12 weeks post TQD and 7-day point prevalence abstinence at 2- and 12-weeks post-quit: nicotine dependence, depression, anxiety, stress, alcohol use, drug use, motivation, and self-efficacy.
7. The following baseline self-report assessment outcomes will predict lower number of cpd and higher number of days abstinent at 2- and 12- week visits: urge, withdrawal symptoms, depression, anxiety, stress, alcohol use, drug use, motivation, and self-efficacy.
8. The following baseline self-report assessment outcomes will predict abstinence on phone-based self-report at 1, 2, 6, 12, 26, and 52 weeks post-TQD urges, withdrawal, motivation to quit smoking or remain abstinent, and confidence in ability to quit or remain abstinent
9. Baseline scores on anxiety, depression, and stress will moderate the effect of allocation to Non-Responder status in the adaptive and standard treatment arms. This finding will show that poor response to pharmacotherapy may be related to high levels of anxiety, depression, or stress.
10. A prospective economic analysis of adaptive vs standard treatment will show cost-benefit outcomes from the perspective of people that smoke cigarettes, healthcare systems, insurance companies, and employers.
11. **Feasibility:** Demographics of patients at DSCP and Duke CSC will reflect the recruitment area
12. **Feasibility:** Medications used will show wide variation of use.
13. **Feasibility:** Attendance at DSCP Return Appointments will be favorable.
14. **Feasibility:** Referral Routes to DSCP will reflect recruitment area.
15. **Feasibility:** Medication side effects will be favorable.
16. **Feasibility:** Medication adherence will be favorable.

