## **3.2 Background and Significance**

**Adaptive Treatment Regimens:** The primary study treatment is a medication strategy referred to here as the adaptive pharmacotherapy algorithm. This strategy uses FDA-approved medications for smoking cessation (Varenicline, Nicotine Patch and Bupropion). Two weeks after starting these treatments, participants are assessed to see how much they have reduced their smoking on these medications. If, after 2 weeks of treatment, participants have reduced their cpd to 50% or less of baseline, they are considered to be “responsive” to treatment and are continued on this treatment alone until 12 weeks post-TQD. After 2 weeks of treatment, participants who have not decreased their cigarette use to 50% or more of their baseline cpd are considered “non-responders”, and Bupropion is added to the treatment regimen 2 weeks prior to the quit attempt and continued until 12 weeks post TQD. Estimates based on prior studies within our lab (see preliminary studies) suggest 50% will be non-responders.

**Pharmacotherapy Control:** The control group used for this algorithm is Varenicline started 1 week prior to TQD (1 week escalating dose) or Nicotine Patch started on the TQD and continuing to 12 weeks post-TQD. This is considered standard of care treatment. P-Varenicline and P-Patch for control participants only will be started 4 weeks prior to TQD, and P-Bupropion will be started 1 week prior to TQD to match study groups

**Behavioral Treatments:** All participants will receive one 40-minute visit with a medical provider who specializes in tobacco dependence treatment.

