### Medication Dosing for Each Group:

#### Varenicline Adaptive Treatment Arm (n=75)

Participants who chose Varenicline-based treatment and are then randomized to the Varenicline Adaptive Treatment Arm will receive the following:

4 weeks prior to TQD: Begin Varenicline with this schedule:

Day 1-3: 0.5 mg q AM for 3 days (with placebo Varenicline in the evening)

Day 4-7: 0.5 mg BID

Day 8 to end of treatment: 1 mg BID

This group will remain on 1 mg BID Varenicline x 3 weeks pre-TQD, then 12 weeks post TQD.

At the 2 week pre-TQD visit, this group will be assessed for “Response” to Pre-quit Varenicline:

**a. Varenicline Non-Responders:** Participants who do NOT show > 50% reduction in cigarettes-per-day from baseline will be continued on Varenicline, and Bupropion will be added as a “rescue medication.”

Bupropion will be added to their regimen 1 week prior to the TQD with this schedule:

Day 1-3: 150 mg q AM

Day 4 to end of treatment: 150 mg BID

Bupropion will be continued for 12 weeks post TQD.

**b. Varenicline Responders:** Participants who show > 50% reduction in cigarettes per day from baseline will be continued on Varenicline as their only active medication.

1 week prior to the TQD, Placebo Bupropion will be added with this schedule:

Day 1-3: 1 placebo pill q AM

Day 4 to end of treatment: 1 placebo pill BID

Placebo Bupropion will be continued for 12 weeks post TQD.

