### **10.7.5. Subject-Rated Standardized Measures to Be Collected at All Clinic Visits**

A number of standardized measures are collected at each clinic visit. All references are listed in each respective appendix. A participant's level of physical nicotine dependence is assessed using the FTND (Appendix 14).

A participant's current withdrawal symptoms from cigarettes is assessed in the MPSS-2 (Appendix 15). Depression is assessed using the PHQ-2 (Appendix 16), anxiety is assessed using the GAD-2 (Appendix 17) and stress is assessed using the PSS-4 (Appendix 18).

Finally, participants will be given a 7 day daily diary to complete prior to in-person study visits. This diary will ask about the number of cigarettes smoked per day and daily medication adherence. Participants will be asked to complete this prior to their visit. If they have not completed the diary prior to the visit, the RA will use the time-line follow-back approach to complete the 7 day diary with the participant. This form can be found in Appendix 20.

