**Nicotine Patch Based Treatment (secondary outcome):** Power calculation for Nicotine Patch Adaptive Treatment vs. Nicotine Patch Standard Treatment is based on abstinence rates observed in prior P50-funded trials. In one trial (Rose et al 2013), when participants received Nicotine Patch prior to their quit attempt, 41.2% showed >50% reduction in cigarettes-per-day (considered Patch Responders) whereas 58.8% did not show >50% reduction in cigarettes-per-day (were considered Patch Non-Responders). "Patch Responders" demonstrated biochemically-confirmed 4-week continuous abstinence at the 11-week post-quit attempt of 59.2%, whereas "Patch Non-Responders," when left on Nicotine Patch alone showed an abstinence rate of 16.0%. When however, the Patch Non-Responders were given Bupropion in addition to Nicotine Patch, they showed an increased abstinence of 28.3%. If our study were to show similar effect sizes as this prior study, the adaptive treatment group with 41.2% responders (abstinence rate = 59.2%), and 58.8% non-responders given Nicotine Patch + Bupropion (abstinence rate = 28.3%), should show an abstinence rate for responders + non-responders of 41.0%. Abstinence rates for Nicotine Patch Standard Treatment in several CSC trials using the similar recruitment and exclusion criteria range from 17-26%. With a conservative assumption that we will see the higher abstinence rates in our controls (e.g. 26%), our two Nicotine Patch-Based Treatment groups should show abstinence rates of **41.2% vs. 26%**. Sample size calculation using 2-tail test with continuity correction assuming  $p = 0.05$  and power = 80%, yields a minimum sample size of **298** in the nicotine patch arm. This study is designed with 150 in the Nicotine Patch arm and so it underpowered to reach this secondary outcome.

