**Varenicline-Based Treatment (secondary outcome):** Power calculation for Varenicline Based Adaptive treatment vs. Varenicline Standard Treatment is based on abstinence rates observed in prior P50-funded trials as well as other published studies. To estimate the effect of adaptive treatment, a critical consideration is that 4 week Varenicline pre-cessation treatment without adaptation was superior to starting 1 week prior to quit day (Hajek et al 2011). Abstinence rate were 20.8% 1-week pre-quit start time. Hajek further showed that for participants starting 4 weeks prior to the Quit day, 35.4% of participants showed >50% reduction in cigs/day with an abstinence rate of 66.7% whereas 64.6% of participants failed to show >50% reduction in cigs/day and had an abstinence rate of 22.6%. The weighted average of these groups = 38.2%. Sample size calculation using **38.2% vs. 20.8%** with 2-tail test with continuity correction assuming  $p = 0.05$  and power = 80%, yields a minimum sample size of **208** within the Varenicline arm alone. This study is designed with 150 in the Varenicline arm and so it underpowered to reach this secondary outcome.

Version Date: 02/26/2020

**Full Sample (Primary Outcome):** Based on these calculations, a sample size of 300 for each of these comparisons should be sufficient to demonstrate significant differences between randomized arms (150 vs. 150). The Primary Outcome is a comparison of 12-week post-TQD smoking abstinence across the study sample (N=300). As stated above, the nicotine patch arm will require n=298 to reach significance, and the varenicline arm will require n=208 to reach significance. Neither arm (150 each) is powered to reach significance. The two arms together (n=300) are powered to reach primary outcomes. For the control group (nicotine patch arm = 26.0%; varenicline arm = 20.8%), an equally weighted sample would result in an abstinence rate of **23.4%**. For the adaptive treatment group (nicotine patch arm = 41.2%; varenicline arm = 38.2%), an equally weighted sample would result in abstinence rate of **39.7%**. A sample size calculation using 2-tail test with continuity correction assuming  $p = 0.05$  and power = 80% results in sample size of **248**. With 300 participants this study as power of 87% power for showing significant results on our primary outcome.

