## Appendix 2: Smoking History

*Please answer the following questions are about your history of smoking, use of other products and medications.*

1. How many cigarettes have you smoked per day, on average? \_\_\_\_\_ [1-99]
2. How many years have you smoked? \_\_\_\_\_ [1-99]
3. Do you usually smoke menthol or non-menthol cigarettes?
  - 1 = Non-Menthol
  - 2 = Menthol
  - 3 = Both
  - 0 = Don't know
4. Which of the following tobacco products have you used in the last week? (Check all that apply)
  - 1 = Cigarettes
  - 2 = Cigars
  - 3 = Pipes
  - 4 = Hookah
  - 5 = Cigarillos
  - 6 = E-cigarettes
  - 7 = Chewing tobacco
  - 8 = Snuff
  - 9 = Other
5. During the last week did you use any of the following drugs? (Check all that apply)
  - 1 = Marijuana
  - 2 = Cocaine/Crack
  - 3 = Meth
  - 4 = PCP
  - 5 = Heroin
  - 6 = Opioids such as Morphine, Oxycotin, Percocet, Vicodini, Fentanyl
  - 7 = Benzodiazepines such as Valium, Xanax, Klonopin
  - 8 = Other

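### Hypothesis 9 draws a conclusion about poor response to drug from the Responder/Non-Responder cut alone, although the cigarette counts behind the cut are already recorded

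*Protocol*

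**What the plan says.** Objective 9 (Protocol, Section 3.1, repeated in the Section 6 table) is "To compare baseline scores on anxiety, depression, and stress for their effect on allocation to Responder or Non-Responder status", asked in both the adaptive and the standard arms. Hypothesis 9 is worded in terms of moderation and closes with a broader reading: "This finding will show that poor response to pharmacotherapy may be related to high levels of anxiety, depression, or stress".

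Section 10.2 defines status by a threshold applied at the visit two weeks before the target quit day. For varenicline: "Participants who do NOT show > 50% reduction in cigarettes-per-day from baseline will be continued on Varenicline", with bupropion then added. The patch arm uses the same threshold.

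The quantities behind the threshold are recorded as numbers. At baseline, Appendix 2 asks "How many cigarettes have you smoked per day, on average", and Appendix 11 asks for daily averages over 7 and 30 days. A 7-day diary precedes in-person visits, of which the Medication Response Visit is one; Section 10.7.5 states: "This diary will ask about the number of cigarettes smoked per day and daily medication adherence".

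No listed analysis takes the pre-quit reduction on its full scale as an outcome. The nearest, hypothesis 7, uses cigarettes per day and days abstinent at the 2- and 12-week visits. Section 13 gives no effect size, sample size or power for objective 9, and leaves exploratory modelling open.

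**The concern.** The cut serves a purpose in the algorithm, since a treatment decision needs a threshold. The closing sentence of hypothesis 9 is about something else: whether people with more anxiety, depression or stress respond less well to the drug. For that question, reductions of 51% and 100% are treated as the same result, and reductions of 49% and 51% as opposite results.

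The threshold is expected to fall near the middle of the distribution. Section 3.2 says prior studies "suggest 50% will be non-responders", and the sample size section cites lower responder shares for each drug. A test on status therefore has less power than a test on the reduction itself, at no saving in data collection. What is at stake is a missed association of modest size, and hypothesis 9 judged unsupported when the data could have supported it.

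**Working it through.** The protocol has no figure for objective 9 to reproduce, so the check compares a test on the full scale with a test on the cut.

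**Inputs from the protocol**
- Responder share p: 50% (Section 3.2), 41.2% for patch and 35.4% for varenicline (Sample Size Calculation).
- Two-sided alpha 0.05 (Section 13).
- n = 150 in the adaptive arms, 300 in total.
- At the Medication Response Visit both standard arms are on placebo. Active varenicline starts one week before the quit day and the active patch on the quit day (Section 10.2). Only the 150 adaptive participants inform response to drug.

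**Assumed, because the protocol is silent**
- Correlation r between a baseline score and the percent reduction, 0.10 to 0.35.
- Approximate bivariate normality.

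**Step 1: information kept by the cut.** Efficiency E = φ(z_p)² / [p(1 − p)], where φ is the standard normal density and z_p the normal quantile of p.
- p = 0.50: 0.3989² / 0.25 = 0.637
- p = 0.412: E = 0.625
- p = 0.354: E = 0.605

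The loss is 1 − E, about 36–40%. With n = 150 the cut test carries the information of about 0.605 × 150 = 91 to 0.637 × 150 = 96 participants analysed on the full scale.

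**Step 2: power.** Full scale: Φ(√(n − 3) · atanh(r) − 1.96). For the cut, replace r by r√E.

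Example, n = 150, r = 0.20. Full scale: √147 × 0.2027 − 1.96 = 0.498, power 69%. Cut at 50%: r√E = 0.20 × 0.798 = 0.160; √147 × 0.161 − 1.96 = −0.01, power 50%.

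| n | r | Full scale | Cut at 50% / 41.2% / 35.4% | Loss (points) |
|---|---|---|---|---|
| 150 | 0.10 | 23% | 16 / 16 / 16% | 7 |
| 150 | 0.15 | 45% | 31 / 30 / 30% | 14–15 |
| 150 | 0.20 | 69% | 50 / 49 / 48% | 19–21 |
| 150 | 0.25 | 87% | 69 / 68 / 67% | 18–21 |
| 150 | 0.30 | 96% | 84 / 83 / 82% | 12–14 |
| 150 | 0.35 | 99% | 94 / 93 / 92% | 6–7 |
| 300 | 0.10 | 41% | 28 / 28 / 27% | 13–14 |
| 300 | 0.15 | 74% | 55 / 54 / 52% | 20–22 |
| 300 | 0.20 | 94% | 79 / 79 / 77% | 15–17 |
| 300 | 0.25 | 99% | 94 / 93 / 92% | 6–7 |
| 300 | 0.30 | about 100% | 99 / 99 / 98% | under 2 |

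Losses are taken from unrounded powers. A simulation with 20,000 replicates per setting, run for cuts at 50% and 41.2% and r from 0.15 to 0.30, agrees to within about one point.

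**Step 3: how far the inputs can be trusted.** Section 9.2 excludes a PHQ-2 score of 3 or more, so the depression score at entry can only be 0, 1 or 2. GAD-2 is an integer from 0 to 6 (Appendix 17). Percent reduction cannot exceed 100% and may be skewed. The powers are therefore approximate, and the narrow depression score makes larger correlations with it less likely.

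**The case against.** The strongest defence is that status is the right outcome. It is the algorithm's own rule for adding bupropion, and which smokers are routed to add-on treatment is a sensible question that only status answers. That stands. A reader might infer that the status comparison should be dropped or reduced to a description; the documents do not support that, and the test on status should stay.

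Second, the objective is exploratory and Section 13 says such analyses are not limited to those listed. A reader might infer that the plan forbids a full-scale analysis; it does not. But the outcome for this question is named in both the objective and the hypothesis, and it is the cut. That is a stated choice, not a detail left for later.

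Third, the size of the loss rests on correlations that the protocol does not give. A reader might take a fixed loss of 10 to 20 points as a property of the plan. The table shows otherwise: the loss depends on r and n, and over all 300 participants, as the objective is worded, it runs from about 22 points at r = 0.15 to under 2 at r = 0.30. Only the share of information lost follows from the protocol's own figures, and that too needs approximate normality.

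Fourth, hypothesis 9 speaks of moderation, which a regression of cigarette change on baseline scores does not test. This is correct. The added analysis answers the hypothesis's closing inference about poor response, not its moderation wording.

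**Conclusion.** The concern holds in a limited form. Objective and hypothesis 9 rest a conclusion about poor response to pharmacotherapy on the Responder/Non-Responder cut alone, although the underlying counts are collected. At responder shares of 35.4% to 50% and under approximate normality, the cut keeps about 61–64% of the information.

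In the 150 adaptive participants this costs about 12–21 points of power if r lies between 0.15 and 0.30, and about 7 points at r = 0.10 or 0.35. These power figures are conditional on assumed correlations and refer to percent reduction, the quantity that is cut.

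The weight is low. No primary or secondary analysis, sample size or treatment decision depends on objective 9.

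**What to change.** In objective and hypothesis 9, separate the two questions.

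- **Response to drug.** Regress change in cigarettes per day, from baseline to the Medication Response Visit diary, on each baseline score. Adjust for baseline cigarettes per day and chosen medication, and restrict to the adaptive arms because the standard arms are on placebo at that visit. Use a rank-based or robust fit if the change is skewed. Name the baseline count, since Appendices 2 and 11 offer more than one.
- **Routing to add-on treatment.** Keep the Responder/Non-Responder comparison as a tested outcome for who the algorithm routes to bupropion.

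The treatment rule itself is not touched.

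The cost is a change of wording and one more exploratory analysis; no new data, visits or participants are needed. The regression coefficient also reads less directly than a chance of non-response, which is a further reason to report the status comparison beside it.
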